### Aims

Our primary aim in this study is to evaluate whether stressed or distressed veterans and active-duty service members experience a greater reduction in suicide risk, suicide urges, the wish to live, and the wish to die when receiving Caring Contacts. We will measure these outcomes through EMA and survey measures of SI and cognitions. The second aim is to examine the experiences of diverse veterans and service members with Caring Contacts (ie, access, satisfaction, and preferences) via qualitative interviews. The third aim is to evaluate if veterans and service members receiving Caring Contacts will show reductions in measures of distress (ie, isolation, depression, substance misuse, loneliness, defeat, hopelessness, and psychological pain). Finally, the fourth aim is to examine potential mechanisms of action for Caring Contacts (ie, mattering, connectedness, social responsibility, and entrapment) measured via EMA.

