#### EMA Study

Participants will receive invite links to complete the EMAs at various time points across the study period, as shown in Table 1. Each EMA point has 10 or 11 items (described in the subsequent section), which usually take 30 seconds to 3 minutes to complete (based on participants enrolled thus far and the pilot testing of the EMAs). All participants will initially receive invitations for 3 daily assessments for 14 days before randomization (42 assessments) to establish baseline mean and variability metrics for the EMA outcomes and mechanisms, and an additional 7 days of EMA (21 assessments) at 12-month follow-up. Participants randomized to conditions that include EMA, following the baseline assessment period, complete 7 days of EMA per month at months 1 to 11 (231 assessments) to assess real-time mean and variability of risk and potential mechanisms (Table 1).

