#### Primary Outcomes (Aims 1.1 and 1.2)

The primary EMA outcomes are mean levels of 3 suicide risk indicators of motivation to live, desire to die, and urges for suicide rated on a Likert scale from 0 to 10 (aim 1.1). The specific items include “How much do you want to die right now?,” “How much do you want to live right now?,” and “How strong are your urges for killing yourself right now?” Higher scores indicate higher suicidal risk (the item regarding motivation to live is reverse-coded). They are assessed at every EMA point throughout the study follow-up period. In the pilot trial of this study, we used visual analog scale (VAS), consisting of a slider on a straight line with end points representing the extremes, to measure these items. Their convenience and ease of rapid administration make them highly compatible with EMA research designs, facilitating efficient real-time data collection in naturalistic settings [59]. VAS of suicide intent [60], suicide desire [61], suicide urges, and perceived burdensomeness [62] were pilot-tested. However, VAS was not found to be user-friendly due to the limitations of the REDCap survey interface when presented on a smartphone. As such, we changed the response options for these suicide risk items to buttons labeled 0 through 10 in place of a VAS from 0 to 100.

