#### Analysis Plan

First, descriptive statistics will be calculated for all variables and group differences in baseline variables will be examined to ensure randomization success. All outcome variables will be examined for nonnormality, and given past suicide research, we anticipate a positive skew for suicidal thoughts and behaviors, and we will use an appropriate model for all analyses based on the distribution of the outcome variables. On the basis of a Directed Acyclic Graph model generated using DAGitty [124,125], demographic variables are conditionally independent of our outcome variables after accounting for the variables specified in our aims and thus do not confound the relationship between the Caring Contacts intervention and our outcome variables. However, to understand the nuanced effects of Caring Contacts on suicide risk across diverse subgroups, we will control for ethnicity, gender, and military status (veteran vs current US military service member) as covariates in our analysis. This stratification allows us to discern potentially differential impacts of the intervention and ensures that our findings are robust and applicable across the varying demographic profiles within the veteran population. Furthermore, all analyses will be conducted using an intent-to-treat framework, using all available data, and using robust maximum likelihood estimation to account for missing data.

For aim 1.1, individual participant means and SDs of each suicide indicator (motivation to live, passive ideation, active ideation, suicide intent, and urges to harm self) will be calculated from the baseline and 12-month EMA period (for all conditions). Then, to assess group differences in the outcome measures of interest, an analysis of covariance examining condition-specific differences at 12 months, controlling for baseline values of the outcome variable of interest, will be conducted. Preplanned post hoc comparisons will compare (1) any Caring Contacts (combined) to no Caring Contacts, (2) Caring Contacts with and without EMA, and (3) EMA with and without Caring Contacts.

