For aim 4, to examine potential mechanisms of Caring Contacts, we will use the within-EMA period data and examine within-participants mediation using dynamic structural equation modeling (with random intercepts and slopes) [130]. Dynamic structural equation modeling allows for the simultaneous estimation of within- and between-person effects that allow for idiographic mechanistic models over time, which can be ideal for answering questions about within-participant mechanisms of suicide outcomes. In line with recommendations for intensive longitudinal data analysis, all hypothesized mechanism variables (ie, mattering, personal and social responsibility, perceived burdensomeness, and entrapment) will be centered at both the between-person and within-person mean level. Then, within-person regression models will be run to examine the relationship between the hypothesized mechanisms and suicide outcome, using a lag-1 model and autoregressive covariance structure to account for assessments closer in time to be more highly correlated. Next, to examine the mediation effect of treatment condition on outcomes through the hypothesized mechanisms, we will estimate within-level indirect mediation effects, calculated as the product of the within-level effect of treatment condition on the mechanism (a path) and the effect of the mechanism on the suicide outcome. All mediation analyses will be examined at the within-person level (1-1-1), excluding cross-level mediation. Random starts will be used for all models to replicate the best log-likelihood. Finally, to examine the immediate versus delayed impact of the timing of Caring Contacts intervention, we will use autoregressive modeling to examine the direct impact on stress, distress, and suicide outcomes immediately following a Caring Contacts message compared to times without a message, using the EMA data. For all regressions, 95% CIs will be reported, and statistical significance will be set at *P*<.05.

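### The aim 1.1 primary EMA outcomes are three item means in the Measures section but means and SDs of five indicators in the Analysis Plan, and two of the five have no described EMA item

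*Protocol article*

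**What the plan says.** Under Primary Outcomes (Aims 1.1 and 1.2) the protocol article states: "The primary EMA outcomes are mean levels of 3 suicide risk indicators of motivation to live, desire to die, and urges for suicide". It gives one item for each: "How much do you want to live right now" (reverse-coded), "How much do you want to die right now" and "How strong are your urges for killing yourself right now", all scored 0 to 10. A suicide intent scale is mentioned there only among the visual analog scales tried in the pilot.

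Under Analysis Plan, the aim 1.1 paragraph computes "individual participant means and SDs of each suicide indicator (motivation to live, passive ideation, active ideation, suicide intent, and urges to harm self") at baseline and at 12 months. It then compares conditions at 12 months by ANCOVA with baseline adjustment, on the outcome measures of interest, followed by three preplanned comparisons. It does not say which of these variables are primary or whether SDs rank below means.

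Other relevant places:
- EMA Study: "Each EMA point has 10 or 11 items".
- Aims: participants are to "experience a greater reduction in suicide risk, suicide urges, the wish to live, and the wish to die" when receiving Caring Contacts. Neither active ideation nor intent is named.
- Analysis Plan, closing sentence: "For all regressions, 95% CIs will be reported, and statistical significance will be set at" P<.05.

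**The concern.** The two sections describe different outcome sets for the same primary aim. One has three variables. The other, as listed, has five indicators times two summaries, which is ten. The labels also differ: passive ideation is not a name used for the want-to-die item, and urges to harm oneself are not the same as urges to kill oneself.

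If this stands, a result on an SD, or on an indicator outside the three, could be reported as a primary finding, and the choice between the lists could be made after the results are known. The point carries weight because the article presents EMA as the trial's primary measure of outcome.

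The Aims sentence adds a smaller problem: read literally, it hopes for a reduction in the wish to live.

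**Working it through.** **1. Matching the indicators to items**

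| Analysis Plan indicator | Described EMA item |
|---|---|
| Motivation to live | want to live (reversed) |
| Passive ideation | plausibly want to die |
| Active ideation | none described |
| Suicide intent | none described (pilot scale only) |
| Urges to harm self | plausibly urges for killing yourself |

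Even with the generous pairings, two of the five are unmatched.

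**2. Item count per prompt**

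Inputs are from Potential Mechanisms of Caring Contacts (Aim 4): burdensomeness 1 item, entrapment 1 item, and one of three rotated scales per prompt (mattering 5, personal responsibility 4, social responsibility 4).

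- Mechanism items: 1 + 1 + 4 = 6, or 1 + 1 + 5 = 7.
- With three suicide items: 9 or 10.
- With five suicide items: 11 or 12.
- Stated under EMA Study: 10 or 11.

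Neither list reproduces the stated count. The three-item list leaves exactly one item undescribed. If that item were a suicide item there would be four, one short of five. So at least one of the five indicators cannot be measured as described.

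**3. Number of outcome variables**

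- Measures section: 3 means.
- Analysis Plan, three items with mean and SD: 3 × 2 = 6.
- With one further suicide item: 4 × 2 = 8.
- As listed: 5 × 2 = 10.

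**4. What the choice does to the false-positive chance**

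Simulation under no effect of Caring Contacts or EMA, with three equal arms (510/3 = 170 each). The contrasts are any Caring Contacts versus none (.5, .5, −1), Caring Contacts with versus without EMA (1, −1, 0), and EMA with versus without Caring Contacts (1, 0, −1). Each is declared significant at |z| > 1.96 with no preceding gate. All variables, means and SDs alike, are given one common correlation r. The article supplies no value, so r is an assumption, shown as a range.

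Chance of at least one P<.05:

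| Variables | r = 0.8, three contrasts | r = 0.4, three contrasts | any-versus-no contrast only (r = 0.8 to 0.4) |
|---|---|---|---|
| 3 | 21% | 28% | 10–13% |
| 6 | 29% | 44% | not needed |
| 8 | 32% | 53% | not needed |
| 10 | 35% | 59% | 17–32% |

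Three contrasts on a single variable already give about 11%.

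**The case against.** The strongest reply is that only the Measures section uses the word primary for EMA outcomes, that the Aims name the same three constructs, and that the Analysis Plan merely says means and SDs will be calculated. On that reading the primary outcomes are the three means and the parenthesis is leftover wording. That may be what was meant. But the five indicators and the SDs stand inside the aim 1.1 analysis, and the exploratory label in the next paragraph covers only the growth analysis in the 340 participants with monthly EMA. Condensing a protocol explains an omission; it does not explain two lists that disagree.

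Several stronger readings are tempting and are not supported:
- *That the primary test as a whole is open.* The ANCOVA, the baseline adjustment, the 12-month time point and the three contrasts are all stated. Only the outcome set and the rank of the SDs are unsettled.
- *That some primary analyses will have no data.* The article says the items include the three it quotes, and the full EMA item list is not shown. What can be said is that no item is described.
- *That the undescribed prompt item must be a fourth suicide item.* The count shows one missing item, not its content. The aim 4 text also analyses stress and distress from EMA data, so it could be one of those.
- *That the ten-variable error rate is the expected one.* If some indicators cannot be measured, ten variables cannot all be tested; 6 to 8 is the realistic range.

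It is also fair that much of the error rate comes from the three contrasts and would remain under the three-mean list, that one contrast tests EMA rather than Caring Contacts, and that a gate by the overall ANCOVA test would lower the figures. The P<.05 sentence closes the aim 4 paragraph, so applying it to each aim 1.1 contrast is an inference. The gap between the lists remains under a gate: with one overall test per variable, and independence assumed, the chance is 1 − 0.95³ = 14.3% for 3 variables and 1 − 0.95¹⁰ = 40.1% for 10.

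**Conclusion.** The concern holds as a contradiction about the primary outcome set, and it should be resolved before analysis. The set is 3 variables by one section and 6 to 8 measurable ones (10 as listed) by the other. Two of the five indicators lack a described item, at least one cannot be measured as described, and the SDs have no rank.

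Moving from 3 to 6–8 variables raises the chance of at least one nominally significant contrast from about 21–28% to about 29–53%. These figures rest on equal arms, ungated contrasts at .05 and an assumed common correlation of 0.4 to 0.8. The item-count argument rests on reading the rotation as one scale per prompt.

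The wording on the wish to live in the Aims is a slip and not an analytic error, because reverse-coding already fixes the direction of the analysis.

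**What to change.** - In the Analysis Plan, replace the five-indicator list for aim 1.1 with the three items of the Measures section (want to live reversed, want to die, urges for killing yourself), means only, as the primary outcomes.
- Label the SDs, and any other EMA suicide item that exists, as secondary or exploratory.
- Under EMA Study, reconcile the count of 10 or 11 with the described items and name the missing one.
- In the Aims, word the wish to live as an increase.

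Naming the contrast that decides aim 1.1 and adding a Holm step over the three means would be useful, but neither is needed to remove the contradiction and both may be left to the SAP.

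The cost is a few lines of text and a check against the registered outcomes. No new data are needed. The article places analysis after data collection, which is projected to finish in July 2026, so the change can be made before results are seen.

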### Data Analysis

#### Power and Sample Size

We plan to recruit 510 participants with the aim of holding type I (α=.05) and type II error rates (β=.05; power=0.95) at equal levels. For aim 1.1 with 3 conditions and 2 assessment time points, a sensitivity power analysis conducted using the *pwr* package in the R software (R Foundation for Statistical Computing) indicated that our proposed sample size will provide sufficient power to detect moderate effect sizes, with the smallest detectable effect size being f^2^=0.17. For aim 1.2, our proposed sample size will provide sufficient power to detect small effect sizes, with the smallest detectable effect size being f^2^=0.03. On the basis of the prevalence rate for SI in US military service members and veterans between 13.9% and 14.1% and between 1.9% and 2.4% for suicide attempts [122], we expect that 13.9% (71/510) of our proposed full sample will report current SI.

For aim 3, comparing the 2 primary conditions (n=340), with a 7-day assessment period and 3 assessments per day (total observations, n=21), power analysis using the *EMAtools* R package shows sufficient power (0.95) to detect moderate (Cohen *d=*0.5) to large (Cohen *d*=0.8) effects within a month at α=.05, even with a 50% response completion rate. For the full year of the monthly 7-day assessment period (total observations, n=252), the same analysis similarly indicates sufficient power to detect moderate to large effects across 12 months. For aim 4, the recommended sample size is for a 2-level mediation model based on Monte Carlo simulations [123] or detecting small effects with adequate power (0.8) while holding the type I error rate at α=.05, when there are at least 3 assessments per participant, are between 215 and 257 participants if within-participant correlations are moderate (intraclass correlation coefficient [ICC]=0.1),300 to 438 participants if within-participant correlations are moderate (ICC=0.4-0.6), and 495 to 544 participant if within-participant correlations are high (ICC=0.9). Notably, as within-participant observations increase, the required sample size to achieve adequate power decreases. With 12 within-participant observations, our required sample size would be smaller than the recommended sample size [123]. Altogether, 510 participants and 252 assessments per participant over the course of the study should provide sufficient power to detect the hypothesized between- and within-participant effects.

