For those participants who will complete EMA for all 12 months (n=340), we will conduct an *exploratory analysis* of changes over time in the mean and intraindividual SD of suicide outcomes. The unique and intensive sampling approach of EMA allows for fine-grained exploration of if and when outcomes change in a clinical trial. Specifically, we will first visually examine trajectories by condition to determine the shape of change *trajectories* over time. Then, following the determination of the shape, we will conduct a linear mixed effects growth model (eg, linear, nonlinear quadratic, and piecewise) [126-129], including a dummy-coded condition variable (with EMA only as the reference) as a predictor of both intercept and slope to determine how intervention condition impacts change in suicide outcomes over time.

For aims 1.2 and 3, to examine secondary suicide outcomes and measures of psychological distress, we will use analysis of covariance to examine condition-specific differences in continuous scores of suicide ideation and cognitions and examine group differences at 12 months, controlling for baseline values of the outcome variable of interest. Similarly, preplanned post hoc comparisons will compare (1) any Caring Contacts (combined) to no Caring Contacts, (2) Caring Contacts with and without EMA, and (3) EMA with and without Caring Contacts. For both aims 1.1 and 1.2, any baseline variables that were not successfully randomized will be included as covariates in the regression models.

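### Near the floor of a 0-10 item the raw within-person SD tends to follow the mean, so the planned SD analyses cannot by themselves support a separate claim about variability

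*Protocol article*

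**What the plan says.** Under Primary Outcomes (Aims 1.1 and 1.2), the protocol article states "The primary EMA outcomes are mean levels of 3 suicide risk indicators", each "rated on a Likert scale from 0 to 10". The SD is not named there.

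The Analysis Plan section uses the SD in two places:

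- **Aim 1.1.** It computes "individual participant means and SDs of each suicide indicator" for the baseline and 12-month EMA periods. An ANCOVA of the 12-month values follows, "controlling for baseline values of the outcome variable of interest, will be conducted". Ethnicity, gender and military status are further covariates, as are baseline variables found to be unbalanced. The 12-month mean is not a covariate in a model for the SD.
- **Exploratory analysis.** In the two arms with monthly EMA (n=340), a mixed-effects growth model is applied to "changes over time in the mean and intraindividual SD of suicide outcomes", with condition predicting intercept and slope.

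On the expected distribution, the same section says "we anticipate a positive skew for suicidal thoughts and behaviors". Power and Sample Size adds "we expect that 13.9% (71/510) of our proposed full sample will report current SI". The plan also undertakes to choose models that suit each outcome's distribution. Nothing in the article models the SD jointly with the mean, adjusts it for the mean, or scales it to what the mean allows.

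**The concern.** On an item that cannot go below 0, level and spread are not free of each other. A person who answers 0 throughout has an SD of 0 whatever drives the answers. If many participants sit close to 0, a treatment that lowers the level moves more ratings onto the floor and compresses the raw SD. A test of the SD can then be significant because the level changed.

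At stake is a second scientific claim. The Background and EMA Study sections present variability as something EMA is well placed to measure. One effect on the level could appear in the report as two findings: lower suicide risk and less variable suicide risk. The second would not have been shown.

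**Working it through.** **The plan's own figure.** 0.139 × 510 = 70.9, so 71, and 71/510 = 13.9%. The other 439/510 = 86.1% are not expected to report current SI. This figure and the expected skew are the article's only evidence that scores lie near 0.

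**The bound.** A 0-10 score with mean m has a maximum SD of √(m(10 − m)), or slightly more with an n − 1 divisor.

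| m | 0.1 | 0.25 | 0.5 | 1 | 2 | 5 |
|---|---|---|---|---|---|---|
| max SD | 0.99 | 1.56 | 2.18 | 3.00 | 4.00 | 5.00 |

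This limits the SD but does not fix it, so its practical force needs simulation.

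**Inputs from the article.** 510 participants allocated evenly to three arms, so 170 per arm; 42 baseline and 21 month-12 prompts; α = 0.05.

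**Inputs assumed because the article does not give them.** Latent normal ratings with constant within-person SD (1.0 or 1.5), rounded and cut to 0-10; 70% completion; a treatment effect on the latent level only, of 0, 0.3, 0.6 or 1.0 points.

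**ANCOVA.** The 12-month SD is regressed on condition (any Caring Contacts v none) and baseline SD, with robust standard errors and 400 runs per cell. The Monte Carlo standard error is √(0.05 × 0.95/400) = 1.1 percentage points at 5%. Rejection rates (%) at latent shifts 0 / 0.3 / 0.6 / 1.0:

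| Control mean (latent SD) | SD test | Mean test |
|---|---|---|
| 0.33 (1.5) | 4.5 / 18.0 / 55.2 / 96.0 | 4.5 / 12.8 / 43.5 / 87.0 |
| 0.42 (1.5) | 4.8 / 29.2 / 77.8 / 99.5 | 5.5 / 22.8 / 70.0 / 98.8 |
| 0.47 (1.0) | 4.8 / 44.0 / 94.5 / 100 | 5.0 / 39.2 / 93.8 / 100 |
| 0.57 (1.5) | 6.0 / 44.2 / 94.8 / 100 | 6.0 / 46.8 / 94.2 / 100 |
| 1.00 (1.5) | 5.5 / 54.5 / 95.8 / 100 | 4.8 / 58.8 / 98.0 / 100 |
| 2.30 (1.5) | 5.5 / 29.8 / 78.0 / 99.8 | 5.8 / 66.2 / 99.5 / 100 |
| 5.00 (1.5) | 4.8 / 6.2 / 5.5 / 9.8 | 4.8 / 85.0 / 100 / 100 |

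In the first five rows the person-level correlation of mean and SD is 0.78-0.83. A latent shift of 0.6 lowers the observed mean there by only 0.10-0.27 points, so the result does not depend on a large visible effect. A separate run with control means of 0.25-0.9 gave SD rejection of 34-46% at 0.3 and 89-93% at 0.6. The pattern also appears when every prompt is answered, so missed prompts do not explain it.

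**Growth analysis.** 340 participants, 12 months, level falling gradually by the stated shift, between-arm difference in person-level slopes of the monthly SD, 200 runs per cell. With control means of about 0.4-1.1, rejection was 3.5-5% at no shift, 62-98% at 0.6 and 93-100% at 1.0. At mid-scale it was 6.5%, 5.5% and 9.5%.

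**Does adjusting for the mean cure it?** Adding the 12-month mean, its square and the baseline mean removes about 80-90% of the spurious SD difference at a shift of 0.6 (for example −0.132 becomes −0.016). Rejection still runs at about 10-27% at 0.6 and 25-63% at 1.0.

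**Does a limit-aware model cure it?** In a small check (150 runs, two scenarios), a location-scale model treating 0 and 10 as limits rejected the variance term in 4% and 7%.

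**The case against.** The strongest counter-arguments, and what stands of each:

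- **Aim 1.1 may not test the SD at all.** The primary outcomes are defined as means, and the article says only that SDs will be calculated before the ANCOVA. This stands: for aim 1.1 an SD test is a possible reading. The growth model names the SD explicitly, but it is labelled exploratory.
- **The floor is inferred.** The 13.9% is a prevalence for service members and veterans in general, whereas this sample is selected for stress or distress, with SI itself a qualifying marker. Reverse-coded motivation to live may sit well above 0. This stands. At a control mean of 2.3 the artefact is still large, but the SD test no longer mirrors the mean test; at mid-scale it almost disappears.
- **A lower mean does not force a lower SD.** This stands. Someone moving from a constant 3 to ratings between 0 and 2 shows a larger SD. The effect is a tendency across participants.
- **Unchanged variability is defined on an unobserved scale.** On the observed scale fluctuation does fall, and describing that is legitimate. This stands for description, but not for reading the fall as an effect separate from the level.
- **Models will be matched to the outcome's distribution.** This deals with skew. A skew-suited model for the SD still analyses a quantity tied to the mean, although the wording leaves room for a better model.

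A reader might infer that the trial will report a false variability effect. The documents do not support that: with no level shift the SD test keeps its 5% size, and the size of any shift is unknown.

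**Conclusion.** The point holds in a limited, conditional form. If the items lie near 0 and the intervention lowers the level, the planned raw-SD analyses can present one level effect as a second effect on variability. With control means of roughly 0.25-1 the chance is about 20-55% at a 0.3-point latent shift and 55-96% at 0.6, against about 5% with no shift and 4-10% at mid-scale. These figures rest on assumed item means, within-person SDs, shifts and a latent-normal model, none of which the article supplies.

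It would be wrong to conclude that the primary result is at risk. The comparison of means is untouched, and the SD test creates no efficacy signal without a true change in level. What needs correcting is the interpretation of a non-primary, partly exploratory measure. That makes this an inexpensive improvement, not a flaw in the trial's main inference.

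**What to change.** In the aim 1.1 and exploratory paragraphs of the Analysis Plan:

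1. Report raw person-level SDs descriptively beside the means, and state that an SD difference will not be read as an effect on variability separate from the level.
2. Base any variability claim on an analysis that separates the two. A suitable choice is a prompt-level location-scale mixed model, ordinal or censored at 0 and 10, with separate condition effects on level and on within-person variance. Draw the claim from the variance term only.
3. As a sensitivity analysis, use a variability index scaled to its maximum given the mean.
4. Do not rely on covariate adjustment for the concurrent mean alone.

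The cost is analysis work on data already being collected. Because the article places analysis after data collection, the change can be specified beforehand. There are two downsides. Power for variability will be lower, since participants at the floor carry little information about it. The result will also depend on the assumed latent distribution: the suggested model was checked only on latent-normal data, so its behaviour under other distributions is not established.
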